**Figure 2 figure2:**
[figure not shown]
Screenshots of the app used in this study. The app for patients has a simple design to help them perform the locomotive training (LT). The app for physicians allows them to check a patient’s LT status based on the ID for that patient. The number of days with LT is displayed on the same screen for both the patient and the physician.

### Outcomes

#### Timeline

The timetable of enrollment, interventions, and assessments is displayed in Table 1, including the quantitative self-reported outcomes and TUG results at the baseline, interim, and final evaluations. Demographic and clinical information will be obtained from the participants’ electronic medical records at baseline and will include their date of birth, gender, BMI, medical history, and disease or diseases causing LS.

**Table 1 table1:** Timetable and evaluation items.

Item	Baseline	4 weeks after DTx^a^ initiation	8 weeks after DTx initiation
Patient consent	✓		
Patient background	✓		
Timed up and go test	✓	✓	✓
25-question Geriatric Locomotive Function Scale	✓	✓	✓
Behavioural Regulation in Exercise Questionnaire 3	✓	✓	✓
Days with locomotion training		✓	✓

^a^DTx: digital therapeutics.

#### Primary Outcome

The primary outcome is TUG test values before and after the DTx intervention. The TUG test is widely used in clinical practice as an outcome measure to assess mobility, fall risk, and dynamic balance in adults, and it can assess objective mobility [21,22]. Furthermore, previous research has shown that patients with LS have significantly longer TUG times than control groups [23]. In patients with rheumatoid arthritis, TUG values are significantly shortened and physical function is improved by continuing LT [24]. We determined that TUG is a useful indicator of the effects of LT for participants with LS.

#### Secondary Outcomes

Secondary outcomes are the participants’ GFLS-25 and BREQ-3 scores. The GFLS-25 is a self-report questionnaire used to assess difficulties and impairments in daily activities related to LS and can be used to assess subjective mobility [5-7]. The BREQ-3 assesses motivation for exercise with 18 questions in 6 areas: intrinsic motivation, integrative adjustment, identification adjustment, incorporative adjustment, external adjustment, and demotivation [25]. The BREQ-3 is used in this study to assess changes in attitudes toward exercise before and after the DTx intervention.

#### Other Clinical Outcomes

We will evaluate the numbers of days LT was performed at 4 weeks and 8 weeks after the intervention, as recorded in the smartphone app.

### Statistical Methods and Sample Size

The primary outcome of this study, TUG test values, will be measured repeatedly in the same participants at 0 weeks before the DTx intervention and 4 and 8 weeks after the intervention. These data will be compared with an ANOVA, with the TUG score as the dependent variable. The secondary outcomes, GLFS-25 and BREQ-3 scores obtained at the 3 time points, will also be compared with an ANOVA. The significance level will be set at .05 / 3 = .0167 with Bonferroni correction.

The minimal clinically important difference in the TUG test for patients with degenerative disc disease has been reported to be 3.4 (SD 5.0) [26]. Considering this finding, we set the minimal clinically important difference at 3 for this investigation. The required sample size was calculated using G*power (Heinrich-Heine-Universität Düsseldorf) [27]. We selected the corresponding *t* test, and we calculated the effect size as 0.6 based on a mean difference of 3.0 and an SD of difference of 5.0. Assuming that α is .05 and power (1 − β) is .80, the required sample size was estimated to be 24. We set the target number of cases for this study at 50, taking into account that the SD might be smaller than in previous studies, some participants might drop out, and other factors.

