**Methods:**

We conducted a multicenter, prospective, longitudinal, nonrandomized, single-group study of Japanese adults aged ≥40 years who were eligible for LS checks. Each participant underwent an 8-week locomotion training (LT) intervention, and their subjective and objective motor abilities and motor awareness were objectively assessed at the following time points: baseline (before the start of the DTx), interim (4 weeks after the start of the DTx), and end (8 weeks after the start of the DTx). We evaluated the participants’ objective motor function using the timed up and go (TUG) test, and we compare the results using a 3-way ANOVA with the TUG test at the 3 evaluation time points as the dependent variable. The results of the 25-question Geriatric Locomotive Function Scale, which is a subjective measure of motor function, and the results of the Behavioural Regulation in Exercise Questionnaire 3, which assesses motor awareness, were also evaluated using an ANOVA in the same way as the TUG test. The significance level was set at .05 / 3 = .0167 after Bonferroni correction.

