### Objectives

The study’s primary aim is to determine whether the use of a smartphone app (ie, DTx) can prevent or ameliorate LS in older people: the outcomes are exercise awareness as assessed by the Behavioural Regulation in Exercise Questionnaire 3 (BREQ-3) and motor function as assessed by the GLFS-25 and timed up and go (TUG) test. In this study, participants who were unable to perform the stand-up test or 2-step test due to hip or knee pain were excluded from the measurement items. The research questions are as follows: (1) Can older people use DTx to proactively change their exercise habits with the help of their health care providers? (2) Are changes in exercise habits in older people associated with changes in motor awareness and function?

Our main and secondary study hypotheses are that (1) continued LT with DTx will prevent or improve LS in older adults and (2) well-established exercise habits will improve these individuals’ motor awareness and function.

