### Study Design

This trial is a multicenter, prospective, longitudinal, nonrandomized, single-group study of Japanese adults aged ≥40 years with applicable LSC results. The design includes 3 evaluation time points: baseline (0 weeks, ie, before the initiation of DTx), an interim evaluation (4 weeks after DTx initiation), and a final evaluation (8 weeks after DTx initiation).

An investigation of DTx that was designed to reduce anxiety about recurrence in postoperative breast cancer patients included a baseline assessment before the DTx intervention, an interim assessment after 4 weeks of intervention, and a final assessment after 8 weeks of intervention [18]. Previous studies have shown that 6 weeks of balance exercise intervention and 2 months of body weight–bearing exercise can improve lower limb muscle strength, balance ability, and walking speed in older people [19,20]. We and other research groups thus consider 4-week and 8-week postintervention assessment time points as appropriate for this type of study.

We registered the trial with the University Hospital Medical Information Network Clinical Trials Registry (UMIN000053922; receipt number R000061550). The date of approval was March 22, 2024.

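### The .0167 level has no stated family and, as written, falls on the single primary outcome, which was sized at .05

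*Protocol article*

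**What the plan says.** All references are to the protocol article.

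- **Primary Outcome** names one measure: "The primary outcome is TUG test values before and after the DTx intervention".
- **Statistical Methods and Sample Size** gives its analysis over weeks 0, 4 and 8: "These data will be compared with an ANOVA, with the TUG score as the dependent variable". It then adds: "The secondary outcomes, GLFS-25 and BREQ-3 scores obtained at the 3 time points, will also be compared with an ANOVA". The threshold follows at once: "The significance level will be set at .05 / 3 = .0167 with Bonferroni correction".
- **Abstract, Methods** repeats the threshold after listing all three measures: "The significance level was set at .05 / 3 = .0167 after Bonferroni correction".
- **Study Design** supplies another possible source of a 3: "The design includes 3 evaluation time points". Three time points give three pairwise comparisons, although no section names any pairwise test.
- **Secondary Outcomes** describes the structure of one secondary instrument: "The BREQ-3 assesses motivation for exercise with 18 questions in 6 areas". The article does not say whether a total or each area is tested.
- The **sample size**, also in Statistical Methods and Sample Size, rests on a paired t test of TUG with a mean difference of 3.0, an SD of the difference of 5.0, alpha .05 and power .80. It requires 24 participants. The target is 50.

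**The concern.** A Bonferroni divisor has meaning only for a named set of tests. Two sets of three are available here, and they lead to different decision rules.

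- If the 3 counts outcomes, the TUG ANOVA is judged at .0167.
- If it counts time pairs within an outcome, the TUG ANOVA could be judged at .05, with .0167 kept for follow-up comparisons.

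A TUG ANOVA p-value of .03 would fail under the first reading and succeed under the second. The study is single-group and unblinded, and nearly all the planned data are already in hand, so that choice should not remain open when the results are seen.

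The second difficulty is internal. With one declared primary outcome, no penalty for the secondary outcomes is needed, yet the stated level imposes one on TUG. The sample size ignores that penalty and uses .05. The stated requirement of 24 and the stated threshold of .0167 therefore do not belong to the same test.

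**Working it through.** **Inputs** (all from the protocol article)

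- Mean difference 3.0, SD of difference 5.0, alpha .05, power .80, required N 24, target N 50: Statistical Methods and Sample Size.
- Complete data sets so far, 45: Results.
- Sidedness is not stated. Two-sided is assumed because it reproduces the plan's figure; one-sided gives 19.

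**Step 1. The threshold.** .05 / 3 = .01667, which rounds to the stated .0167.

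**Step 2. The plan's sample size.** The effect size is d = 3.0 / 5.0 = 0.6. For a paired t test with n pairs, the noncentrality is d × √n on n − 1 degrees of freedom. Power is the probability that a noncentral t variable exceeds the two-sided critical value in absolute size. At alpha .05 and n = 24, the noncentrality is 0.6 × √24 = 2.939, the critical value is 2.069 and power is 80.4%. With n = 23, power is 78.5%. The required N is therefore 24, as stated.

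**Step 3. The same calculation at .0167.**

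| n | Noncentrality 0.6 × √n | Critical t at .0167 | Power at .0167 | Power at .05 |
|---|---|---|---|---|
| 24 | 2.939 | 2.582 | 64.1% | 80.4% |
| 31 | 3.341 | 2.536 | 78.4% | 89.8% |
| 32 | 3.394 | 2.531 | 80.0% | 90.8% |
| 45 | 4.025 | 2.489 | 93.3% | 97.6% |
| 50 | 4.243 | 2.479 | 95.8% | 98.6% |

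The smallest n with 80% power at .0167 is 32. That is 8 more than the plan's 24, an increase of 8 / 24 = 33%.

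**Step 4. What a divisor of 3 covers.** For k independent tests at .0167, the chance of at least one false positive is 1 − (1 − .05/3)^k. For k = 3 this is 4.9%, with a Bonferroni bound of 5.0%. The divisor therefore works for three outcome-level ANOVAs. It also works for three time pairs within one outcome: a null simulation with 45 participants gave about 4% to 4.5% for that case.

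It would not cover both families at once. Three outcomes by three pairs is 9 tests, with a Bonferroni bound of 9 × .0167 = 15%; the simulation, which allows for the dependence between time contrasts, gave 10% to 13%. This last case is an assumption, because the article plans no such set of 9 tests. It shows only why the family has to be named.

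**The case against.** **The divisor does fit something.** The threshold comes directly after three outcomes, each with one ANOVA, and the plainest reading is one test per outcome. That reading controls the error rate at 5% across the three. This stands. The fault is a missing label and a mismatch with the sample size; the number itself is a possible one.

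**The power cost is small.** The target of 50 and the 45 complete data sets both exceed 32. This also stands, under the plan's effect size, and it limits the weight of the point.

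**An article may leave detail to a fuller document.** That is fair for post hoc comparisons and for questionnaire scoring. It does not excuse two different alphas for the same outcome in one section.

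A reader might also infer several stronger charges that the article does not support:

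- *That error is inflated across many pairwise or BREQ-3 area tests.* No pairwise test and no area-level test is stated, so any such count is the reader's own. Secondary outcomes also need no joint control with a single primary outcome unless confirmatory claims are to rest on them.
- *That a summed BREQ-3 score would cancel opposing changes.* No summed total is described.
- *That Objectives contradicts Primary Outcome.* Objectives says "the outcomes are exercise awareness as assessed by the Behavioural Regulation in Exercise Questionnaire 3 (BREQ-3" and goes on to GLFS-25 and TUG. It lists measures that serve the primary aim and calls none of them the primary outcome, so the two sections are compatible.

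**Conclusion.** The point holds in this limited form. The protocol sets .0167 without naming the family it protects, and as written it applies that level to a single primary outcome sized at .05. The stated requirement of 24 matches .05; at .0167 it would be 32, and 24 would give 64.1% power instead of 80.4%. Enrolment already exceeds either figure, so the study is not underpowered for this reason.

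The figures assume a two-sided paired t test with a true standardised change of 0.6, as in the plan's own calculation. They do not describe the power of the ANOVA that is to be used, for which the article gives no inputs. The ambiguity over the decision rule does not depend on these assumptions.

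**What to change.** Make a dated amendment before the data are analysed. Results says that no analysis has yet been done.

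1. Name one primary test: TUG at 8 weeks versus baseline, at two-sided .05. This matches the paired t test and the alpha in the sample-size calculation.
2. Apply Bonferroni or Holm only to a stated family of secondary tests. Set the divisor to the number of tests in that family, and count each BREQ-3 area if areas are tested separately.
3. If .0167 is kept for TUG, say what the 3 counts and restate the required sample size as 32.
4. Make the same change in the abstract.

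**Cost.** No new data and no further recruitment are needed. Secondary tests may face a stricter threshold than .0167 if their family has more than three members. The change also relaxes the primary threshold and replaces an ANOVA with a named contrast, at a time when 45 data sets have been collected without blinding. The amendment must therefore give its reason and record that it was made before anyone analysed the outcomes.

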## Methods

### Participants and Study Setting

We plan to recruit a minimum of 50 participants aged ≥40 years who are eligible for LSCs [14] at any of 3 general hospitals (Bange-Kosei General Hospital, Southern Tohoku General Hospital, and Minami-Soma City General Hospital) that perform orthopedic surgery. The target minimum numbers of participants is 25 at Bange-Kosei General Hospital, 15 at Southern Tohoku General Hospital, and 10 at Minami-Soma City General Hospital. The overall recruitment target is based on the minimum sample size necessary to complete the intended analysis, taking omissions into account.

The study’s inclusion criteria are as follows: participants aged ≥40 years who generally have lower-extremity muscle weakness [15] and who have visited 1 of the 3 abovementioned hospitals for an LSC, which are scored as follows: 1 point if the individual cannot put on a sock on one foot; 2 points if they stumble in their house; 3 points if they need a handrail to climb stairs; 4 points if they have difficulty using a vacuum cleaner at home; 5 points if they have difficulty carrying parcels weighing >2 kg; 6 points if they have difficulty walking continuously for >15 minutes; and 7 points if they cannot cross a crosswalk with a green light. Additional inclusion criteria are scoring ≥3 points on the Mini-Cog cognitive functional assessment [16,17], having access to the smartphone app, and being able to provide informed consent for study participation. The exclusion criterion was difficulty using smartphone apps due to cognitive decline or visual or hearing impairment.

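### The required sample size of 24 is computed at alpha .05, but the plan tests at .0167, where 80% power on the same paired contrast needs 32; the target of 50 still suffices

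*Protocol article*

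**What the plan says.** Under Statistical Methods and Sample Size, the TUG test is the primary outcome, measured at 0, 4 and 8 weeks: "These data will be compared with an ANOVA, with the TUG score as the dependent variable". The secondary outcomes, the 25-question Geriatric Locomotive Function Scale and the exercise-motivation questionnaire, are handled the same way. The first paragraph ends: "The significance level will be set at .05 / 3 = .0167 with Bonferroni correction". The Methods part of the abstract repeats this: "The significance level was set at .05 / 3 = .0167 after Bonferroni correction". Neither place exempts TUG, and neither says whether the divisor of 3 counts outcomes or pairs of time points.

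The next paragraph gives the sample size. The test and effect size are stated as "We selected the corresponding *t* test, and we calculated the effect size as 0.6". Behind that effect size stand an assumed average change of 3.0 and a standard deviation of 5.0 for the change. The error rates are "Assuming that α is .05 and power (1 − β) is .80", and the result is "the required sample size was estimated to be 24". The target is then raised to 50. The reasons given concern the SD, dropout and other unnamed factors; the corrected alpha is not among those named.

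Under Participants and Study Setting, the article adds: "The overall recruitment target is based on the minimum sample size necessary to complete the intended analysis, taking omissions into account". The Results section reports, as of April 2025, 47 participants who agreed, 45 complete data sets, and no analysis yet done.

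**The concern.** One section gives two alphas for what appears to be the same primary comparison: .0167 for the test and .05 for its sizing. A sample size and its power describe a test only at the alpha used to compute them. If TUG is judged at .0167, the pairing of 24 participants with 80% power is not a property of that test.

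Two things are at stake. First, the stated minimum is too low for the plan's own threshold, so the reserve between it and the target looks larger than it is. Second, the level that governs the primary test is left open to argument. A TUG p-value between .0167 and .05 would be a success under one sentence and a failure under the other.

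**Working it through.** **Inputs, all from Statistical Methods and Sample Size.** Mean difference 3.0; SD of the difference 5.0; sizing alpha .05; power .80; test level .05 / 3 = .0167. The targeted number (50) is from the same section and the complete data sets (45) from Results. Sidedness is not stated.

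**Effect size.** dz = 3.0 / 5.0 = 0.6, as stated.

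**Formula.** For a paired t test with n participants, df = n − 1 and the noncentrality is dz × √n. Two-sided power is the probability that a noncentral t variable falls outside ± the critical t value at that alpha.

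**Reproducing the plan's figure (two-sided .05).**
- n = 23: power 78.5%.
- n = 24: noncentrality 0.6 × √24 = 2.939, critical t (23 df) = 2.069, power 80.4%.

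So 24 is the smallest n that reaches 80%, exactly as stated. A one-sided test at .05 would need only 19, so the calculation was two-sided.

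**Same contrast at the plan's test level (two-sided .0167).**

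| n | Noncentrality | Critical t | Power |
|---|---|---|---|
| 24 | 2.939 | 2.582 | 64.1% |
| 31 | 3.341 | 2.536 | 78.4% |
| 32 | 3.394 | 2.531 | 80.0% |
| 45 | 4.025 | 2.489 | 93.3% |
| 50 | 4.243 | 2.479 | 95.8% |

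The required number is 32, which is 8 more than stated (8 / 24 = one third). The reserve up to the target is 50 − 32 = 18, not 50 − 24 = 26.

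**The three-time-point ANOVA, as a sensitivity check.** The documents give no mean at week 4 and no correlation structure, so these are assumptions: sphericity, SD of any difference 5 (error variance 25 / 2 = 12.5), and a total change of 3 s. The noncentrality is n × (sum of squared deviations of the three means) / 12.5, with 2 and 2(n − 1) df. The sum of squares is 4.5 for a linear change (0, −1.5, −3) and 6.0 if the whole change is present by week 4 (0, −3, −3).

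| n | Power at .0167, linear | Power at .0167, full change by week 4 |
|---|---|---|
| 24 | 55% | 71% |
| 45 | 89% | 97% |
| 50 | 92% | 98% |

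Under these assumptions 80% power needs 37 or 29 participants respectively. On either pattern 24 falls short, while 45 and 50 do not.

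**The case against.** The strongest reply is that nobody plans a trial of 24. The target is 50 and 45 complete data sets are in hand. Both keep power above 90% on the paired contrast at .0167, so no enrolment decision changes. This stands, and it makes the point minor. A reader who sees 64% might infer that the trial is underpowered; the article's own target rules that out on its own assumptions.

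It can also be said that the arithmetic is right for its stated inputs, since .05 is printed in the same sentence as 24. That stands too: the fault is an inconsistency between two stated levels, not a miscalculation. It does not remove the fault, because .0167 is stated for the analysis without exempting TUG. The unexplained divisor does not help either. Whether 3 means outcomes or pairs of time points, a baseline versus 8-week TUG comparison would be judged at .0167.

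A reader might go further and treat sizing by a t test as an error in itself, because the analysis is an ANOVA. The documents do not support that as a separate fault. Sizing a repeated-measures study on its key paired contrast is ordinary practice, and the Primary Outcome section defines the outcome as TUG before and after the intervention. The corrected figure of 32 is also a paired-test figure, and the ANOVA range rests on mean patterns and sphericity that the article does not give.

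Nor does Participants and Study Setting call 50 the bare statistical minimum. It says the target is based on a minimum and allows for omissions, which can be read as a minimum plus a reserve. Finally, one might fear that the figure would mislead the sizing of the proposed randomised study. The Discussion already gives about 200 per group for that study, and nothing links it to this calculation.

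**Conclusion.** The point holds as a minor inconsistency. At the plan's own level of .0167, the stated 24 participants give 64.1% power for the sized contrast rather than 80%, and the matching requirement is 32. The study as targeted is adequately powered: 95.8% at 50 and 93.3% at 45 for the paired contrast, and about 92–98% and 89–97% for the assumed ANOVA.

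These figures rest on a two-sided test (the only sidedness that reproduces 24), the article's mean difference of 3.0 and SD of the difference of 5.0, and .0167 applying to TUG as written. The ANOVA figures also need the assumptions stated with the calculation.

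**What to change.** Keep .0167 and restate the calculation at that level under Statistical Methods and Sample Size. Suggested wording: *For the baseline versus 8-week paired TUG contrast at two-sided .0167, with a mean difference of 3.0 and an SD of the difference of 5.0, 80% power requires 32 participants; the target of 50 gives about 96%, and 45 complete cases about 93%.*

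Add that this sizes the paired contrast and not the omnibus ANOVA. Under Participants and Study Setting, make clear that 50 is this minimum plus a reserve.

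Do not resolve the conflict by moving the primary test to .05. That would make 24 correct for a single declared contrast, but it would loosen a published threshold after data from 45 participants have been collected.

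The cost is a few sentences of wording and a slightly less favourable stated minimum (32 rather than 24). No extra participants are needed. The Results section says the analysis has not been run, so the correction can still be made before results are seen.
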